#### Primary outcome measures

The primary outcome measures of effectiveness in the comparison of the two interventions are:

Case detection delay, measured in months since the first signs or symptoms of leprosy until diagnosis and in the number of patients with grade 2 disability.Number of new patients with leprosy, subdivided into child proportion, female proportion and multibacillary/paucibacillary classification.Number of contacts screened and receiving SDR-PEP.

#### Secondary outcome measures

Feasibility will be assessed by looking at outcome measures related to cost-effectiveness and acceptability (table 3):

A cost-effectiveness analysis will be undertaken in the third year of the project, encompassing the costs incurred by the health system and the beneficiaries (out-of-pocket expenditure). It will include collecting indicators such as unit costs, costs per case detected, costs per disability-adjusted life years averted and costs per extra case found. The current practice ‘routine service provision’ will be compared with the two study interventions.The acceptability of both interventions will be determined by comparing the number of index patients and contacts included, as well as by using qualitative research methods, such as semi-structured interviews guided by topic lists, focus group discussions (FGDs) with relevant stakeholders and potentially ethnographic observations during the interventions for further data validation. More in-depth (country-specific) protocol descriptions on the acceptability and cost-effectiveness side-studies will be developed together with health economist(s) and social scientist(s).

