	Primary: Number of contacts who received chemoprophylaxis	The community-based intervention will allow more contacts to be screened and receive SDR-PEP compared with the health centre-based household contact approach	Number of contacts screened; number of contacts who received SDR-PEP	Descriptive statistics
1.2 To compare the feasibility of the two chemoprophylaxis interventions (screening household contacts or screening contacts via skin camps) in terms of cost-effectiveness and acceptability	Secondary: Cost-effectiveness of each intervention	The community-based intervention will be more expensive but will have a greater impact compared with the health centre-based household contact approach	Number of index patients included; number of contacts screened; number of cases prevented; number of disabilities avoided; operational costs; out-of-pocket expenses	Health economic evaluations
	Secondary: Acceptability of each intervention	Both interventions will be accepted in participating countries	Number of index patients included; number of contacts screened; and qualitative outcomes	Descriptive statistics; qualitative content analysis of interviews; FGDs and potentially observations
2.1 To assess the acceptability of an integrated skin diseases approach and the use of the SkinApp	Additional: Number of contacts diagnosed with other skin diseases	The community-based intervention will identify more cases of other skin diseases from contact screening compared with the health centre-based household contact approach	Number of contacts diagnosed with skin diseases and with NTDs that manifest with skin lesions	Descriptive statistics; Pearson’s χ^2^ test; Fisher’s exact test; multivariate logistic regression analysis
	Additional: Acceptability of an integrated skin screening approach and the use of the SkinApp	The integrated skin screening approach will encourage screening participation, and the SkinApp will help health workers to diagnose skin diseases	Number of contacts diagnosed with skin diseases and with NTDs that manifest with skin lesions; utilisation of the SkinApp during contact screening; and qualitative outcomes	Descriptive statistics; sensitivity and specificity; positive and negative predictive values; qualitative content analysis of interviews, FGDs and potentially observations

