### Sample size

The sample size calculation was based on case detection delay as the main outcome measure for comparing the effectiveness of each intervention. This measure was used for the calculation because the epidemiological impact (ie, reduction in overall new case detection rate in PEP4LEP districts) will not become apparent within the study duration due to the long incubation time of leprosy. The mean or median delay will be compared between both interventions and with the baseline. A baseline case detection delay will be estimated in each country by interviewing recently diagnosed patients with leprosy with the same structured questionnaire prior to the start of the study. For the sample size calculation, a literature-based estimated average case detection delay of 24 months for patients with leprosy with a SD of 8 months was used, with the conservative assumption that a minimal delay difference of 3 months would be detected between both interventions.^73 74^ In order to achieve this, we aim to include at least 675 index patients in the study: 270 in the community-based intervention areas (30 per country per year) and 405 new patients in the health centre-based intervention areas (45 per country per year). Approximately 100 contacts will be screened per index patient in the community-based intervention areas, and approximately 6 contacts will be screened per index patient in the health centre-based intervention areas; thus, a total of approximately 30 000 contacts will be screened (figure 3). We expect no major differences in case detection delay between clusters and within clusters, hence no significant design effect is foreseen. For the feasibility study component and additional research objectives, interviews and FGDs are planned. For the interviews, a minimum of 10 index patients, 10 household contacts, 10–20 community contacts, 10 health workers/community volunteers, 4 health decision-makers and 10 community leaders will be included. For the FGDs, 6–10 participants will be included: two groups of index patients, two groups of household contacts, two groups of community contacts, two groups with health workers and one to two groups with decision-makers. Contacts refusing to receive skin screening and/or take SDR-PEP, but who are willing to participate in the qualitative study component and community members outside of the 20 closest houses to the index patient in intervention one will also be included. The qualitative research sampling will be purposive, according to the defined target groups, and balanced according to, for example, gender, age, education level, religion and/or socio-cultural background. All fully trained health staff involved in the PEP4LEP project will be asked to consent to enrol in the capacity assessment.

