
### Randomisation

PEP4LEP used randomisation without blinding at the (clustered) health centre level (health centres/posts), ensuring that clusters were similar in size. There are 17 health facilities included in Ethiopia, 22 in Mozambique and 23 in Tanzania. Blinding is not possible because of the varying operational components of the interventions. Cluster randomisation is commonly used when trying to capture the impact of an intervention at community level on both infectiousness and susceptibility.^75^ This method is stated to be feasible logistically, and contamination (eg, information-sharing between participants from both interventions) is unlikely.^75^ Randomisation was performed using the statistical software package R.^76^ Per country, health centres were randomly divided into the community-based intervention or health centre-based intervention.

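### The quantitative part of the acceptability outcome compares raw counts that follow the arms' recruitment aims and contact definitions, so it does not measure acceptance

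*Protocol article*

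**What the plan says.** All references are to the protocol article.

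- **Measure.** Secondary outcome measures: "The acceptability of both interventions will be determined by comparing the number of index patients and contacts included". The sentence goes on: "as well as by using qualitative research methods, such as semi-structured interviews guided by topic lists, focus group discussions (FGDs) with relevant stakeholders". Table 3, under objective 1.2, lists the same two counts (index patients included, contacts screened) together with qualitative outcomes, to be analysed by descriptive statistics and content analysis. Neither place gives a denominator of people approached, invited or eligible.
- **Planned index patients.** Sample size: "we aim to include at least 675 index patients in the study", made up of "270 in the community-based intervention areas (30 per country per year) and 405 new patients in the health centre-based intervention areas", where the second aim corresponds to 45 a year in each country.
- **Planned contacts.** The same section plans about 100 contacts screened per index patient in the camp arm and about 6 in the health-centre arm, roughly 30,000 in all. The sections on the two interventions explain the gap: camps draw on the 20 nearest houses, the health-centre arm on one household.
- **Hypothesis.** Table 3: "Both interventions will be accepted in participating countries".
- **Further detail.** "More in-depth (country-specific) protocol descriptions on the acceptability and cost-effectiveness side-studies will be developed".

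**The concern.** Acceptability is about how people respond when an intervention is offered to them. A count of those included reflects that response, but also how many were asked. Here the number asked differs between arms by plan: the index-patient aims are in the ratio 2:3, and the two arms define a contact differently. The quantity to be compared therefore mostly reproduces the plan.

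Two features add to the difficulty. Table 1 sets arm-specific conditions for index patients: in the camp arm, permission for a camp; in the health-centre arm, having household contacts and being willing to inform them. Refusing such a condition is the very signal sought, and it is invisible in a count of those included. Also, the number of contacts screened is already a primary effectiveness measure, on which Table 3 expects the camp arm to be higher. Using the same count for acceptability mixes reach with acceptance.

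The Objectives section makes comparison of feasibility a primary study objective, and Table 3 assesses feasibility through cost-effectiveness and acceptability. A reader of the results could take a larger count as greater acceptance, and would get opposite answers from the two counts.

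**Working it through.** **Inputs** (Sample size section): 30 and 45 index patients per country per year; 3 countries; totals of 270, 405 and 675, which imply 3 years; about 100 and about 6 contacts per index patient; about 30,000 contacts in total.

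**Step 1: reproduce the plan's figures.**
- Camp arm: 30 × 3 × 3 = 270 index patients.
- Health-centre arm: 45 × 3 × 3 = 405 index patients.
- Sum: 270 + 405 = 675, as stated.
- Contacts: 270 × 100 = 27,000 and 405 × 6 = 2,430. The sum, 29,430, is within 2% of the stated 30,000.

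**Step 2: the comparison if both arms just meet their aims.**

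| Count | Camp | Health centre | Camp ÷ health centre |
|---|---|---|---|
| Index patients | 270 | 405 | 0.67 |
| Contacts | 27,000 | 2,430 | 11.1 |

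The first row favours the health-centre arm 1.5-fold (405/270), the second the camp arm 11-fold.

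**Step 3: can the index-patient count reveal willingness?** Number approached = number included ÷ uptake. The uptake values below are assumptions; the document gives none.

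| Assumed uptake, camp / health centre | Approached, camp / health centre | Included |
|---|---|---|
| 50% / 50% | 540 / 810 | 270 / 405 |
| 70% / 70% | 386 / 579 | 270 / 405 |
| 90% / 90% | 300 / 450 | 270 / 405 |
| 90% / 60% | 300 / 675 | 270 / 405 |
| 60% / 90% | 450 / 450 | 270 / 405 |

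Equal acceptance, better acceptance of camps and better acceptance of health-centre screening can all give the same pair of counts. Only included ÷ approached tells them apart.

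**Step 4: can the contact count?** With 270 camps, the camp total would equal the other arm's 2,430 only at 2,430 / 270 = 9 contacts per camp. Against the roughly 100 people to be invited to each camp, that is about 9% attendance. Above that level the camp arm has the larger count even though most invited people may have stayed away. Dividing by index patients does not help: 100 / 6 = 16.7 is simply the ratio of the two contact definitions. This step does not depend on how the clusters were divided between arms.

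**The case against.** The strongest defence has four parts.

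1. *Acceptability does not rest on counts alone.* Correct. Interviews, focus groups and possibly observations are planned, and contacts who refuse screening or prophylaxis may be interviewed. That is a real strength, but purposive interviews cannot say what fraction refused, so the quantitative comparison stays as it is.
2. *Detail is deferred to side-study protocols.* Also correct, and those protocols may supply denominators. But the article has already named the measure, twice, and says the numbers will be compared. The point concerns a definition that is stated, not one that is missing.
3. *The hypothesis is not directional.* True, but objective 1.2 is to compare the two interventions, and raw counts cannot show that either was accepted.
4. *About 100 and about 6 give a yardstick for attendance.* Only loosely. The camp figure is used both for people invited and for people screened, whereas 6 is the number expected to attend. Neither is a recorded denominator.

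A reader might go further and infer that the targets are fixed quotas, so that the design strictly sets the result. The documents do not support that: 675 is a minimum aim, and actual inclusion may depart from it.

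Nor do they support the inference that, with "ensuring that clusters were similar in size", an even 337.5 index patients per arm was to be expected and that 270 against 405 contradicts it. The Randomisation section gives no number of clusters per arm. A split of the 62 facilities near 25 to 37 would yield 2:3 (62 × 0.4 = 24.8), and similar size need not mean similar leprosy caseload. Testing the gap as if it were random error is meaningless, because aims have no sampling error.

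The further inference that a third of camp-arm patients would go without a camp also fails. It needs an even split and a cap at 270, neither of which is stated, while the section on the camp intervention ties a camp to each diagnosis.

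**Conclusion.** The point holds for the quantitative part of one secondary outcome. The counts to be compared are largely driven by arm-specific aims (270 against 405 index patients) and contact definitions (27,000 against 2,430 contacts). If those aims are met, the counts favour opposite arms, 1.5-fold and 11.1-fold, irrespective of willingness.

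The index-patient part assumes inclusion close to the stated minimum aims. The contact part is firmer, since it follows from what each intervention offers and needs no assumption about cluster allocation. The primary outcome, case detection delay, is not affected.

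**What to change.** In Secondary outcome measures and in Table 3, replace the raw counts with three uptake proportions per arm:

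- index patients consenting, among eligible registered patients approached;
- contacts attending, among those invited (residents of the 20 nearest houses, or household members);
- contacts accepting single-dose rifampicin, among those found eligible for it.

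For the first proportion, define the denominator by the criteria common to both arms. A patient who declines a camp, or who declines to inform the household, then counts as a refusal. Report patients without household contacts separately.

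Give the proportions and their difference with confidence intervals that allow for clustering by health centre and for country, within which randomisation was done. Keep the counts as measures of reach under the primary outcomes, and keep the qualitative component. Because the invited populations differ, describe the contact proportions as uptake of each intervention as offered.

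The cost is small: a log at each site of the numbers approached, invited and eligible, and a change to one outcome definition. No extra patients are needed. The log should start as early as possible, because refusals are hard to reconstruct afterwards.

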#### Additional objectives

The additional objectives are to assess the acceptability of integrated skin screening and the use of the SkinApp as a supporting mHealth tool in the field, as well as health workers’ capacity regarding the integrated skin screening approach (table 3). This will be measured by the number of contacts diagnosed with skin diseases and NTDs and by recording the use of the SkinApp during contact screening. The capacity of health workers to diagnose leprosy and other skin diseases will be determined by a series of four assessments in which the SkinApp can be used: before (baseline) and after PEP4LEP training, during the study and at the end of the study. The four assessments were designed in collaboration with an educational specialist and each include 30 questions (20 multiple choice questions on leprosy and 10 skin disease cases of which five formulated as open questions). The primary PEP4LEP health worker training is conducted over several days and consists of interactive training modules focusing on: the PEP4LEP research project, integrated skin screening including the use of mHealth tools (NLR’s SkinApp and Siilo), clinical leprosy and the administration of SDR-PEP.^4 27 28 30 58 60 61^ Refresher trainings will also be organised. In addition to the assessments, qualitative methods including semi-structured interviews, FGDs and potentially ethnographic field observations will be used to gain a more in-depth understanding of these objectives.

### Case detection delay

Case detection delay is defined by Muthuvel *et al* as the number of months between the onset of signs and symptoms of leprosy and the time of diagnosis, including both ‘patient delay’ (period in months between noticing the first sign/symptom to the first healthcare provider consultation) and ‘health-system delay’ (period in months between the first healthcare provider consultation and the patient receiving the leprosy diagnosis).^62^ Several studies have investigated delay in leprosy diagnosis in countries like Bangladesh, Brazil, India, Colombia and Paraguay.^62–69^ However, recent literature on delay in diagnosis is limited and mainly focuses on other geographical regions. Therefore, delay will be determined with a structured questionnaire that was designed in the project countries along with input from several stakeholders, which will be shared open access (publication expected). The questionnaire includes two annexes: a set of clinical photos of signs of leprosy and a context-specific calendar indicating important local dates, such as festivities, agricultural seasons and religious celebrations.^70 71^ A ‘Question-by-Question Guide’ was designed to provide support in the administration of the questionnaire. The questionnaires were culturally validated in all three countries, based on the conceptual framework of Herdman *et al* (publication expected).^72^

### Sample size

The sample size calculation was based on case detection delay as the main outcome measure for comparing the effectiveness of each intervention. This measure was used for the calculation because the epidemiological impact (ie, reduction in overall new case detection rate in PEP4LEP districts) will not become apparent within the study duration due to the long incubation time of leprosy. The mean or median delay will be compared between both interventions and with the baseline. A baseline case detection delay will be estimated in each country by interviewing recently diagnosed patients with leprosy with the same structured questionnaire prior to the start of the study. For the sample size calculation, a literature-based estimated average case detection delay of 24 months for patients with leprosy with a SD of 8 months was used, with the conservative assumption that a minimal delay difference of 3 months would be detected between both interventions.^73 74^ In order to achieve this, we aim to include at least 675 index patients in the study: 270 in the community-based intervention areas (30 per country per year) and 405 new patients in the health centre-based intervention areas (45 per country per year). Approximately 100 contacts will be screened per index patient in the community-based intervention areas, and approximately 6 contacts will be screened per index patient in the health centre-based intervention areas; thus, a total of approximately 30 000 contacts will be screened (figure 3). We expect no major differences in case detection delay between clusters and within clusters, hence no significant design effect is foreseen. For the feasibility study component and additional research objectives, interviews and FGDs are planned. For the interviews, a minimum of 10 index patients, 10 household contacts, 10–20 community contacts, 10 health workers/community volunteers, 4 health decision-makers and 10 community leaders will be included. For the FGDs, 6–10 participants will be included: two groups of index patients, two groups of household contacts, two groups of community contacts, two groups with health workers and one to two groups with decision-makers. Contacts refusing to receive skin screening and/or take SDR-PEP, but who are willing to participate in the qualitative study component and community members outside of the 20 closest houses to the index patient in intervention one will also be included. The qualitative research sampling will be purposive, according to the defined target groups, and balanced according to, for example, gender, age, education level, religion and/or socio-cultural background. All fully trained health staff involved in the PEP4LEP project will be asked to consent to enrol in the capacity assessment.

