### Outcomes

The primary objectives of this study are to identify the most effective and feasible approach for screening contacts of patients with leprosy in combination with administering chemoprophylaxis to prevent leprosy (table 3). Because of the long incubation period of leprosy, it will not be possible to observe reduced transmission at the population level, in terms of a reduced new case detection rate, during this project period. The active case finding component and raised awareness, however, are expected to lead to more detected cases, improved early case detection and disability rates at time of diagnosis. We hypothesise that enhanced case finding and integrated skin screening will lead to an overall reduction of detection delay primarily in the community-based intervention over the study duration, driven by the diagnosis of patients with early signs of leprosy (and shorter delays) that would otherwise go undetected.

**Table 3 T3:** PEP4LEP project outcomes and methods of analysis

Objective	Outcome	Hypothesis	Outcome measure	Method of analysis
1.1 To compare the effectiveness of a skin camp prophylaxis intervention with a health centre-based prophylaxis intervention in terms of the rate of patients with leprosy detected and delay in case detection	Primary: Case detection delay	Reduction in case detection delay is expected to be greater in the community-based intervention compared with the health centre-based household contact approach	Number of months since first signs or symptoms of leprosy until diagnosis (including assessing both ‘patient delay’ and ‘health-system delay’); G2D percentage among newly diagnosed patients with leprosy	Descriptive statistics; multivariate models; non-parametric tests
	Primary: Number of contacts diagnosed with leprosy	The community-based intervention will identify more cases of leprosy from contact screening compared with the health centre household contact-based approach	Number of contacts diagnosed with leprosy; child proportion; female proportion; MB/PB classification of newly diagnosed patients with leprosy	Descriptive statistics; Pearson’s χ^2^ test; Fisher’s exact test; multivariate logistic regression analysis

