### Data analysis

Data from the PEP4LEP study will be analysed primarily through quantitative methods using descriptive analysis for all variables (table 3). Mean or median case detection delays will be compared between both interventions and the established baseline. This includes newly diagnosed cases identified through each contact screening intervention as well as those detected through ongoing passive case finding, currently the primary method of detection in routine leprosy programmes in the three countries. The p values for each statistical test will be two-tailed with p≤0.05 considered significant and 95% CIs presented for regression analyses. Quantitative analysis will be conducted using statistical software such as SPSS.^79^

The acceptability and capacity assessments will include qualitative research data (table 3), which will be coded and analysed using computer-assisted qualitative data analysis software, including Atlas.ti.^78 80^ Data coding is necessary to categorise and define what the data signify by identifying concepts, patterns, relations and themes.^81^ Data reanalysis will occur until no new topics are emerging and data saturation is reached, which means that no significant new themes are emerging.^82^

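### The comparison with the pre-study baseline is uncontrolled and should be descriptive only; the randomised between-arm difference should be the named primary test, analysed by country

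*Protocol article*

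**What the plan says.** Table 3 of the protocol article states the primary hypothesis as a change: "Reduction in case detection delay is expected to be greater in the community-based intervention compared with the health centre-based household contact approach". The Sample size section sets the target on a different quantity, a 3-month difference in delay between the two interventions, assuming an "estimated average case detection delay of 24 months for patients with leprosy with a SD of 8 months".

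The baseline comes from interviews held before the study starts: "A baseline case detection delay will be estimated in each country by interviewing recently diagnosed patients with leprosy with the same structured questionnaire". No split by arm or health centre is described, and no number of interviews is given.

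Two sections place the comparison with baseline beside the between-arm comparison without ranking them. The Sample size section says "The mean or median delay will be compared between both interventions and with the baseline"; the Data analysis section says "Mean or median case detection delays will be compared between both interventions and the established baseline". Data analysis then applies a two-tailed p≤0.05 to each test. It also says that follow-up delay covers cases found by contact screening as well as by passive case finding, the latter being the main route of detection in routine programmes.

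On design, the Randomisation section says: "Per country, health centres were randomly divided into the community-based intervention or health centre-based intervention". The methods listed for delay in Table 3 are "Descriptive statistics; multivariate models; non-parametric tests", with no covariates named.

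**The concern.** The hypothesis concerns a reduction, the sample size concerns a level, and the baseline comparison is given the same standing as the randomised one. An arm that falls significantly from baseline could then be reported as evidence for the intervention. Two other explanations are built into the design:

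- **Calendar time.** The baseline precedes follow-up, so any secular change in detection is carried into the contrast.
- **Case mix.** Baseline patients come from routine detection, which is mainly passive. Follow-up patients include some found by screening. Adding cases with short delays lowers the mean even if no passively found patient is diagnosed sooner.

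Separately, the stated comparison of means or medians does not mention country, although country is the randomisation stratum and the Study setting section says that the countries differ in endemicity. Nor does it use the baseline interviews to improve the between-arm estimate.

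**Working it through.** **1. The plan's own figures.** Community arm: 30 × 3 countries × 3 years = 270. Health centre arm: 45 × 3 × 3 = 405. Total 675, as stated. No power is stated. With SD 8, difference 3, two-sided 0.05 and no clustering:

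SE = 8 × √(1/270 + 1/405) = 0.63 months; power = Φ(3/0.63 − 1.96) = 99.8%.

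Within one country (90 against 135) the power is 78.7%.

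**2. What a shared country baseline does.** Let B be a country's baseline, and F1 and F2 the follow-up means in the camp and health centre arms. The difference in reductions is (B − F1) − (B − F2) = F2 − F1. B cancels, and the SE stays at 0.63. The randomised contrast is unharmed and gains nothing from B.

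**3. The arm-versus-baseline contrast.** Its expectation is the intervention effect plus any time trend plus the case-mix shift. If a share p of follow-up cases is found by screening with mean delay d, and passively found cases stay at 24 months, the mean falls by p × (24 − d). In the extreme case d = 0, a share of 3/24 = 12.5% gives a 3-month fall with no change among passively found patients; larger d needs a larger share. Nothing in this contrast separates the three parts.

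**4. Leaving out country.** Country means are not given, so two spreads are assumed, with SD 8 taken as the within-country SD (variance 64).

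| Assumed country means | Between-country variance | Share of total variance | Bias at planned mix | Bias if camp arm accrues 40:30:20 and the other arm equally |
|---|---|---|---|---|
| 21/24/27 | 6 | 6/70 = 9% | 0 | 23.33 − 24 = −0.67 months |
| 18/24/30 | 24 | 24/88 = 27% | 0 | 22.67 − 24 = −1.33 months |

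For the second row, (40×18 + 30×24 + 20×30)/90 = 22.67. A bias of 1.33 months is 44% of the 3-month target. Bias is zero at plan because every country contributes 30:45. The cost there is an SE that is too wide: with between-country SDs of 3, 6 and 9 months, power without country in the analysis is 99.4%, 96.8% and 88.7%, still ignoring clustering.

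**5. Using the baseline as a covariate.** Clusters: 17 + 22 + 23 = 62, assumed 31 per arm, so m = 270/31 = 8.7 and 405/31 = 13.1 patients per cluster. Let b be the baseline interviews per centre and r the correlation of true cluster means over time (assumed 0.8). The proportional cut in the variance of the difference is

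(r × ICC)² / {[ICC + (1 − ICC)/b] × V}, where V is the average over arms of ICC + (1 − ICC)/m.

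b is not stated. Planned accrual is 675/62/3 = 3.6 patients per centre per year. If recently diagnosed means six months (the preference given for index patients, assumed here for baseline), b is about 1.8.

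| ICC (assumed) | b ≈ 1.8 | b = 5 | b = 10 |
|---|---|---|---|
| 0.05 | 2% | 5% | 8% |
| 0.10 | 6% | 12% | 18% |
| 0.20 | 14% | 26% | 33% |

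**6. Why not test a difference in changes.** With separate baselines of size b1 and b2 by arm, SE = 8 × √(1/270 + 1/405 + 1/b1 + 1/b2). Power is 30%, 57%, 79%, 92% and 97% when baseline samples are 10%, 25%, 50%, 100% and 200% of follow-up, against 99.8% for the follow-up difference alone.

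**The case against.** The strongest reply is that the trial already plans a concurrent randomised comparison, powers on it, and needs no baseline by arm. Randomisation within country makes expected baseline delay equal, so a greater reduction and a shorter follow-up delay are the same thing in expectation. This stands. A reader might infer that only two before-after comparisons remain, or that a shared baseline defeats the hypothesis; the Sample size and Data analysis sections and step 2 show otherwise.

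Three further inferences are also unsupported:

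- **Baseline collected by country only.** The text describes a country estimate but does not say that facility goes unrecorded.
- **Country excluded from the analysis.** Table 3 lists multivariate models without naming covariates, and an analysis plan that is not shown may include country.
- **COVID-19 falling between baseline and follow-up.** The baseline interviews are not dated, and the Ethics section says that the pandemic emerged while the project was still being developed.

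It can also be said that finding early cases is the intended mechanism, so a case-mix shift is part of the effect. Between arms that is right, because the mix follows from the randomised strategy. Against a historical baseline it cannot be told apart from other changes.

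Finally, the magnitudes in steps 4 and 5 rest on assumed inputs, and power is ample before clustering. That limits the urgency, but it does not justify giving the baseline comparison inferential standing.

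**Conclusion.** The point holds in limited form. The between-arm comparison of follow-up delay is valid and is the contrast on which the sample size rests. The comparison with baseline is uncontrolled, yet it stands beside that contrast under the same p≤0.05 rule; it cannot support an intervention effect.

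Not using country has no bias at the planned 30:45 split. Drift in country mix would introduce one: about 0.7 to 1.3 months under the assumed spreads and a 40:30:20 drift. Not using the baseline interviews gives up about 2–8% of variance at ICC 0.05 and 14–33% at ICC 0.20, assuming correlation 0.8 and roughly 2 to 10 interviews per centre. These are modest gains, worth taking because they cost almost nothing.

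**What to change.** - Name the randomised between-arm difference in delay as the primary test, and reword the Table 3 hypothesis as a shorter delay in the community-based arm.
- Estimate it in one model with country as a fixed effect and health centre (the randomised cluster) as a random effect.
- Where a baseline interview can be linked to a health facility, add the cluster baseline mean as a covariate. Do not switch to a difference in changes.
- Report each arm's change from baseline with an interval but no test, label it descriptive, and show screened and passively found cases separately.

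The cost is a few lines of wording, slightly more analysis work and a facility code on the baseline form. No additional baseline interviews are required.
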